	**Variables**
Primary outcome	Peak TQ at 60°/s of knee extension/flexion (right/left)
Secondary outcomes	ASM/height^2^ (ASMI), ASM/weight x 100 (SMI), Total body fat (%), Trunk body fat (%), Hand grip strength (kg), Creatinine, Pyruvate, Lactate, and high sensitivity C-reactive protein

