**Materials and methods:**

A randomized controlled trial is conducted on 80 adults aged 50–80. A total of 80 participants will be enrolled in this study. Participants assign IOE-taking group (*n* = 40) and placebo taking group (*n* = 40). At a baseline and 12 weeks after treatment, the following parameters of the participants are checked: knee extension strength, handgrip strength, body composition, laboratory tests, dietary recall, physical activity, and EQ-5D-5L.

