### Outcomes

All outcomes were measured at baseline and after 12 weeks. The primary outcome measure was the change from the baseline in the peak torque (TQ) at 60°/s of knee extension/flexion representing muscle function at 12 weeks of IOE or placebo use. The secondary outcome measures were changes in appendicular skeletal mass (ASM)/height^2^ (kg/m^2^) (appendicular skeletal mass index, ASMI), ASM/weight x 100 (skeletal muscle mass index, SMI), total body fat (%), trunk body fat (%), hand grip (kg), serum creatinine, pyruvate, lactate, and high sensitivity C-reactive protein during the 12-week treatment period.

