### Muscle strength

Measurements of knee extension strength representing muscle strength and handgrip strength were conducted using the Biodex System 3 Pro isokinetic dynamometer (Biodex, Inc.) and a Jamar hydraulic hand dynamometer (Performance Health, Warrenville, IL, USA), respectively. The detailed measurement was described in our previous study (13).

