### Statistical analyses

Shapiro–Wilk's test will be used for the normality distribution assessment of all variables (Table 3). A *p* < 0.05 will be considered statistically significant. Data will be analyzed using IBM SPSS Statistics 22.0 (IBM Inc., Armonk, NY, USA) and R software version 3.6.2 (http://www.r-project.org/). Intention-to-treat analysis will be primary for comparisons of outcomes between the IOE and placebo groups, with multiple imputation of missing data. Five imputed data sets will be created for missing values at the 12-week follow-up for all variables. The outcome also will be compared between the two groups using a per-protocol (PP) analysis. Intergroup comparisons of baseline characteristics will be performed using the 2-sample *t*-test or Mann-Whitney's *U*-test for continuous variables and the chi-square test or Fisher's exact test for categorical variables. ANCOVA or rank ANCOVA will be used for the primary analysis, with adjustments for the variables if there is a difference between the two groups at the start of the study and there is a difference in exercise and diet during the study period, all of which will be calculated as a delta. All randomized patients exposed to at least one dose of study intervention will be included for safety analyses, as our previous study (13).

**Table 3 T3:** Study variables.

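### The primary outcome is not fixed as one variable: the article names up to four knee-torque measures, with no rule for choosing, combining or adjusting them

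*Protocol article*

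**What the plan says.** Four places in the protocol article bear on what is primary, and they do not agree.

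- **Table 3 (Study variables), primary outcome row:** "Peak TQ at 60°/s of knee extension/flexion (right/left"). Two movements by two legs is up to four measures.
- **Outcomes:** the primary outcome measure, in the singular, is "the change from the baseline in the peak torque (TQ) at 60°/s of knee extension/flexion representing muscle function". Both movements are named and no leg is mentioned.
- **Muscle strength:** "Measurements of knee extension strength representing muscle strength and handgrip strength were conducted". Neither flexion nor side appears.
- **Abstract, Materials and methods:** the parameter list has "knee extension strength, handgrip strength, body composition". Again extension only.

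On testing, Statistical analyses says that a p-value "< 0.05 will be considered statistically significant" and assigns ANCOVA or rank ANCOVA to the primary analysis. The article does not say which of the measures decides the trial, whether they are averaged or ordered, whether alpha is shared, or whether one or all must succeed.

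**The concern.** A primary outcome is named in advance so that the variable carrying the trial's claim cannot be picked after the results are known. Here a later report could put forward extension alone, flexion alone, one leg, or a mean of legs, and each choice could be squared with some part of the article. If the report treated any one significant measure as success, the stated 5% would not be the error rate of the claim that the extract improves muscle strength.

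A statistical analysis plan may properly hold the multiplicity method. Which variable is primary is a protocol decision. This article does make that decision, but with different content in different sections.

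**Working it through.** **Step 1: count the measures.** Table 3: 2 movements × 2 legs = 4. Outcomes: 2 movements, side unstated. Muscle strength and the abstract: extension only, side unstated.

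**Step 2: inputs.** The threshold is 0.05 (Statistical analyses); two-sided is assumed, because sidedness is not stated. The article gives no correlation between the measures, so a range is shown. It states no familywise error rate, so there is no figure of its own to reproduce.

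**Step 3: false-positive rate if any one significant measure counts.** For k independent tests the rate is 1 − 0.95^k.

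- k = 4: 1 − 0.8145 = 18.5%.
- k = 2: 1 − 0.9025 = 9.75%.

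For correlated tests, equicorrelated normal statistics were simulated (1,000,000 draws, each tested at two-sided 0.05):

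| Pairwise correlation | Any of four | Multiple of 5% | Any of two | Multiple of 5% |
|---|---|---|---|---|
| 0 (formula) | 18.5% | 3.7 | 9.75% | 1.95 |
| 0.5 | 15.6% | 3.1 | 9.0% | 1.8 |
| 0.8 | 11.4% | 2.3 | 7.8% | 1.6 |
| 0.9 | 9.4% | 1.9 | 7.05% | 1.4 |

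A structured case (right with left 0.8, same leg 0.6, opposite leg and movement 0.5) gives 13.4% for four measures. With four measures the multiple falls below 2 once the common correlation exceeds about 0.87.

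**Step 4: other rules that also fit the text.** If all measures must be significant, the rate stays at or below 5%. If the measures are averaged into one score, there is one test and the rate is 5%.

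**Step 5: cost of adjusting instead of choosing.** Sample size determination says that 40 per group already allows for 20% dropout, so about 40 × 0.8 = 32 per group are evaluable. Power of 80% is an assumption, because the article gives none. In units of the SD of the analysed change, the detectable difference is (z(1−α/2) + z(0.80)) × √(2/32), where √(2/32) = 0.25.

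- α = 0.05: (1.960 + 0.842) × 0.25 = 0.70 SD.
- α = 0.0125 (0.05/4, the first Holm step): (2.498 + 0.842) × 0.25 = 0.83 SD.

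For a true difference of 0.70 SD in a given measure, power at 0.0125 drops from 80% to about 62%. Restoring 80% would take about 46 evaluable per group, or 46/0.8 = 57.5, rounded up to 58 enrolled.

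**The case against.** A reader might infer that the plan runs four separate tests at 0.05 and so has a false-positive rate two to four times the nominal level. The documents do not support that. No section says that four tests are run or that one is enough. Outcomes speaks of one measure, Statistical analyses speaks of one primary analysis, and Table 3 is a list of variables, not a testing scheme. An average over legs, a single named leg, or a requirement that all succeed would each fit the text. The multiple also depends on an unstated correlation. Independence, which gives the highest modelled figure, is implausible for two legs of the same person. This objection stands: the inflation is conditional and its size is unknown.

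It can also be said that the article is condensed and refers outcome selection and measurement detail to earlier studies, so a rule for the legs or for multiplicity may sit in the full protocol or analysis plan. That is fair for the alpha rule, and the absence of such a rule is not counted as an error by itself. The abstract's list and the sentence in Muscle strength are also abbreviated, so naming extension alone there is weaker evidence of conflict than the difference between Outcomes and Table 3. But a document not shown cannot make these sections agree with each other, and nothing in this article tells the reader which measure decides the trial.

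**Conclusion.** The point holds as a defect in how the primary outcome is defined. The article gives up to four measures in one place, two in another and one in two others, with a single threshold and no rule linking them.

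The consequence for the error rate is conditional. If any one of four at two-sided 0.05 counted as success, the false-positive rate would be about 9% (correlation 0.9) to 18.5% (independent). With two measures it would be about 8% to 10% (correlation 0.8 to 0). It would not exceed 5% under an all-must-succeed rule or with an average. These figures assume normal test statistics with a common non-negative correlation, which the article does not supply. The article does not establish that the trial's error rate is inflated; it leaves open a reading under which it would be. Because this is the variable on which the trial's claim rests, it should be settled before the results are known.

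**What to change.** Before unblinding, reconcile the abstract, Outcomes, Muscle strength and Table 3, and name one primary variable. One workable choice is the change from baseline to week 12 in knee-extension peak torque at 60°/s, averaged over the right and left legs, with flexion and the single-leg values secondary. Extension is the movement that the abstract and Muscle strength already name. Other single variables, or one composite defined in advance, would serve equally well for error control.

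If all four measures are to stay primary, state in Statistical analyses that they are tested with Holm's procedure (first threshold 0.0125).

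Cost: no new data or visits, but a protocol amendment and a matching update of the registry entry, not just an edit of wording. With a single extension variable, a benefit confined to flexion or to one leg could not be a primary claim. With Holm, the first-step detectable difference rises from about 0.70 to 0.83 SD (80% power and 32 evaluable per group assumed), which favours the single variable at this sample size.

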	**Covariables**
Demography	Age, Gender, Height (cm), Weight (kg), Body mass index (kg/m^2^), Alcohol consumption (per week, amount of alcohol at once), Smoking status (pack, years), Co-morbidities
Vital sign	Blood pressure (mmHg), Heart rate (rpm)
Additional chemistry	Free fatty acid, Creatinin kinase, Tumor necrosis factor-α, interleukin-6, Malondialdehyde, HOMA-IR
Self-Administered Questionnaires	Nutrition assessment (24-h recall method), Quality of life (EQ-5D-3L, VAS), Physical activity (IPAQ), waking log

TQ, torque; ASM, appendicular skeletal mass; ASMI, appendicular skeletal mass index; SMI, skeletal muscle mass index; HOMA-IR, Homeostatic Model Assessment for Insulin Resistance; EQ-5D-3L, Euro-QoL-5 dimensions-3 levels; VAS, visual analgue scale; IPAQ, International Physical Activity Questionnaire.

## Discussion

Muscle loss is a lifelong process that begins around the age of 30. During this process, the amount of muscle tissue and the number and size of muscle fibers gradually decrease. Sarcopenia refers to decreased skeletal muscle, mainly distributed in the extremities. The result of sarcopenia is a gradual loss of muscle mass and strength (1). Sarcopenia can make you vulnerable to arthritis or falls and increase your risk of senility, disability, fractures, and death (5–7). The leading causes of sarcopenia include inadequate nutrition, impaired muscle adaptation to nutrition, mitochondrial dysfunction, oxidative stress, excessive mitochondrial autophagy, changes in hormone production and sensitivity, decreased neuroendocrine regulation, chronic inflammation, and decreased physical activity (2–4). A balanced intake of amino acids-rich milk, eggs, meat, and fish, flexibility and balance, resistance strength training, and endurance training help prevent muscle loss. In addition, various nutrient supplements as an available alternative are being tried to verify their effectiveness on muscle mass, muscle strength, and even physical function in adults with sarcopenia through preclinical and clinical trials.

The main active components of IOE are polyphenols-ishophloroglucin A (IPA) and diphlorethohydroxycarmalol (DPHC) (25). Previous studies revealed that IOE has anti-obesity and anti-diabetic properties (16–18). Although the exact mechanism IOE prevents sarcopenia has not been elucidated, several attempts have been made to clarify the mechanism (18–20). Various genes activate the catabolic pathway of skeletal muscle as age (25). According to studies, phosphatidylinositol 3-kinase (PI3K)-p85α and protein kinase B (Akt), which are involved in muscle proliferation, are down-regulated in sarcopenia with age (26, 27). Recently, systematic preclinical studies have been conducted to verify the effects of IOE or its active components on muscle health (17–22). Jayawardena et al. (22) found that IOE inhibited the adverse effect of lipid-impaired skeletal myogenesis *via* reversion of downregulation of phosphorylation of PI3K/Akt/mammalian target of rapamycin axis, which is responsible for protein synthesis. Yang et al. (28) reported that IPA and IO-derived IPA increased leg muscle width and grip strength in the DEX-induced muscle atrophy model compared with saline. In addition, PI3K mRNA levels were elevated in the soleus muscle tissues in the IPA group. Ryu et al. (21) found that IOE and its active component DPHC improved grip strength and ladder climbing responses and preserved lean mass of calf muscle atrophy induced by dexamethasone (DEX) *in vivo*. Also, treatment with IOE or DPHC restored the DEX-mediated reductions in PI3K and Akt mRNA levels in the gastrocnemius muscle, which increased protein synthesis. PI3K/Akt signaling pathway is a crucial pathway regulating protein synthesis and muscle hypertrophy. Then, this effect was verified in an *in vivo* aging model. IOE or DPHC recovered lean mass, decreased calf circumference, and improved physical activity such as grip strength and ladder climbing in sarcopenic 14-month-old female C57BL/6J mice. IOE and DPHC showed high reversibility for aging parameters such as 17β-estradiol levels and senescence-associated secretory phenotypes levels in 14-month-old female mice. Furthermore, they improved the muscular regeneration-related gene expressions of PI3K/Akt in calf muscle (22).

Based on previous *in vitro* and animal studies, our study aimed to verify that IOE increases muscle mass and muscle strength in humans. We designed a randomized, placebo-controlled clinical trial to assess the effects of IOE on muscle strength, muscle mass, and muscle biomarkers in adults with relatively low muscle mass. IO has been used as food in some Asian regions (29–31). Although a diet containing seaweeds is not common in Western countries, after many benefits of seaweed are revealed, seaweed begins to consume raw materials for healthy food (32). Through this study, it may be possible to recommend using IOE as a nutrient therapy for patients with sarcopenia. However, this study has some limitations; our study focused on middle-aged and elderly Asian subjects and was conducted in a single center, so the effect of IOE on people of varying ages and ethnicities is still unknown. Secondary, a 24-h dietary recall self-questionnaire assesses nutritional intake: this information may not include the everyday diet of participants. Lastly, this is a 12-week follow-up study, so it could not determine the long-term effect of IOE. Despite these limitations, this study has considerable value for the following reason. To the best of our knowledge, the current study will be the first randomized, double-blind, placebo-controlled trial to examine the efficacy and tolerability of IOE supplementation in adults with relatively low muscle mass. The nutritional intake and physical activity that might influence muscle strength and mass will be considered as covariates for transparency of results. The results of this study will provide clinical evidence for sarcopenia patients with nutrient treatment.

## Ethics statement

The studies involving human participants were reviewed and approved by the Ethics Committee of the Institutional Review Board at Pusan National University Yangsan Hospital. The patients/participants provided their written informed consent to participate in this study.
